## Abstract

**Background:**

Although evidence had demonstrated the effectiveness of smartphone apps in diabetes care, the majority of apps had been developed for type 2 diabetes mellitus (T2DM) patients and targeted at populations outside of China. The effects of applying a smartphone app with structured education on glycemic control in type 1 diabetes mellitus (T1DM) are unclear. A digital, culturally tailored structured education program was developed in a smartphone app (Yi tang yun qiao) to provide an automated, individualized education program aimed at improving self-management skills in patients with T1DM in China. This trial aims to investigate the effectiveness of this smartphone app among Chinese T1DM patients.

**Methods and analysis:**

This single-blinded, 24-week, parallel-group randomized controlled trial of a smartphone app versus routine care will be conducted in Changsha, China. We plan to recruit 138 patients with T1DM who will be randomly allocated into the intervention group (automated, individualized education through an app) or routine care group. The intervention will last for 24 weeks. The primary outcome will be the change in glycated hemoglobin (HbA1c) from baseline to week 24. The secondary outcomes will include time in range, fasting blood glucose, levels of serum triglycerides and cholesterol, blood pressure, body mass index, quality of life, diabetes self-care activities, diabetes self-efficacy, depression, anxiety, and patient satisfaction. Adverse events will be formally documented. Data analysis will be conducted using the intention-to-treat principle with appropriate univariate and multivariate methods. Missing data will be imputed with a multiple imputation method under the “missing at random” assumption.

**Discussion:**

This trial will investigate the effectiveness of an app-based automated structured education intervention for Chinese patients with T1DM. If the intervention is effective, this study will provide a strategy that satisfies the need for effective lifelong diabetes care to reduce the disease burden and related complications resulting from T1DM.

**Trial registration:**

ClinicalTrials.gov NCT04016987. Registered on 29 October 2019.

## Data set

**Table Taba:** 

Data category	Information
Primary registry and trial identifying number	ClinicalTrials.gov: NCT04016987
Date of registration in primary registry	29 October 2019
Secondary identifying numbers	N/A
Source(s) of monetary or material support	National Key R&D Program of China
Primary sponsor	The Second Xiangya Hospital
Secondary sponsor(s)	N/A
Contact for public queries	XL, MD, [contact], email: [contact]
Contact for scientific queries	XL, MD, The Second Xiangya Hospital, Central South University, Changsha, China
Public title	An automated structured education intervention based on a smartphone app in Chinese patients with type 1 diabetes: protocol for a randomized controlled trial
Scientific title	An automated structured education intervention based on a smartphone app in Chinese patients with type 1 diabetes: a protocol for a single-blinded randomized controlled trial
Countries of recruitment	China
Health condition(s) or problem(s) studied	Type 1 diabetes mellitus
Intervention(s)	1. Automated, individualized education group: automated, individualized education based on through a smartphone app; 2. Routine care group: education through health-care professionals in the outpatient department
Key inclusion and exclusion criteria	Inclusion criteria: individuals with a T1DM duration of over 6 months who own a smartphone and are capable of using a smartphone app and WeChat, treated with multiple daily injections or an insulin pump, aged 18–50 years, and HbA1c > 7%. Exclusion criteria: being pregnant, having mental disorders, having other conditions or chronic complications related to T1DM, and already using a smartphone app to manage diabetes.
Study type	Interventional; Allocation: randomized; Intervention model: paralleled assignment Masking: single-blind (outcomes assessor) Primary purpose: treatment; Phase: N/A
Date of first enrolment	November 2020
Target sample size	138
Recruitment status	Recruiting
Primary outcome(s)	Hemoglobin A1c level (time frame: 24 weeks)
Key secondary outcomes	Physiological parameters, psychosocial outcomes, and psychological outcomes (time frame: 24 weeks)

## Strengths and limitations of this study

➢ The smartphone app evaluated in this trial was developed in a theoretical- and evidence-based manner and contains a digital culturally tailored structured education program specifically targeted at T1DM patients in the Chinese population.

➢ In combination with artificial intelligence technology, automated, individualized education was offered to a group of patients to explore whether tailoring education materials provided to patients might enhance the effects of the smartphone app.

➢ Treatment effects will be measured with a wide spectrum of outcomes, including physiological parameters, psychosocial outcomes, and psychological outcomes, to capture the complex nature of type 1 diabetes.

➢ To avoid potential bias induced by a lack of blinding, we will use an objective outcome (HbA1c) as the primary outcome and will ensure blinding of outcome assessors.

➢ The generalizability of the results generated from this trial will need to be assessed through multicenter trials.

## Background

Persistent glycemic control is one of the key treatment objectives in the management of type 1 diabetes mellitus (T1DM) to prevent patients from developing and experiencing progression of microvascular and macrovascular complications that lead to disability and premature death [1]. Although insulin injections are effective evidence-based strategies for treating T1DM [2], the management status of T1DM is far away from optimal. For example, according to the data from the T1D Exchange Clinic Network, the percentages of patients achieving the glycated hemoglobin (HbA1c) target set by the American Diabetes Association (ADA) ranged from 14% (18–25 years old) to 30% (26–49 years old) among T1DM patients in the USA in 2014 [3]. Poor T1DM control leads to a heavy disease burden, and it accounted for 964.3 years lived with disability (YLDs) per 1000 globally in 2017 [4]. The situation is even worse in China. According to limited data from hospital-based T1DM patients, there were 3.8 events of diabetic ketoacidosis per 100 patient years among T1DM patients who had a disease duration of more than 1 year [5].

To optimize the benefits of insulin, skills aimed at mastering the adjustment insulin doses are essential and emphasize the important role of diabetes self-management education (DSME) program. Over the past 20 years, DSME programs had been shown to be efficacious and cost-effective in improving patients’ knowledge, skills, and motivation, all of which had contributed to the improvement of biomedical, behavioral, and psychosocial outcomes. For T1DM patients, evidence had demonstrated that structured education programs (SEPs) were the most effective strategy among various DSME programs [6]. However, the implementation of SEP was not optimal due to the complexity of the educational materials and lack of resources (e.g., skill, time, and staff) [7]. Furthermore, even after the successful implementation of SEPs that helped patients improve blood glucose control and quality of life [8], the results from studies with longer follow-up durations showed that HbA1c rebounded 1–3 years after a SEP [9], suggesting that the traditional face-to-face group education model could not satisfy the need for lifelong blood glucose management in T1DM patients.

In the digital era, mobile health can be a possible solution for overcoming the drawbacks of the traditional education model. Evidence had demonstrated the therapeutic effects of smartphone apps for diabetes, with the majority of them being targeted at type 2 diabetes mellitus (T2DM) [10]. A recent systematic review identified seven randomized controlled trials (RCTs) that assessed the effectiveness of smartphone apps in controlling HbA1c in T1DM patients, with five apps specifically targeted at T1DM patients and two targeted at both T1DM and T2DM patients [11]. Pooled results indicated that compared to usual care, patients in the smartphone app group showed a significant reduction in HbA1c (pooled mean difference [MD] − 0.49%, 95% confidence interval [CI] − 0.94 to − 0.04%, *I*^2^ = 83.29%, 7 RCTs), with significant heterogeneity and low quality of evidence. Additionally, only one RCT [12], in which the app was not specifically targeted at T1DM patients, was conducted in China. This implies that an intervention based on internet and mobile medicine that is specifically targeted at the Chinese T1DM population in an evidence-based and culturally tailored manner is urgently needed for improving type 1 diabetes care in China.

A smartphone app with multiple functions (Yi tang yun qiao - The cloud bridge between clinicians and patients) aimed at facilitating a SEP and diabetes control for T1DM patients in the Chinese population was developed by our research team [13]. A needs assessment using mixed methods was used to collect quantitative and qualitative data from both diabetologists and T1DM patients regarding the functions that should be included in a diabetes app [13]. Then, a theoretical- and evidence-based app targeted at T1DM patients was successfully developed [13]. The incorporation of a digital SEP curriculum in the app is one of the main features of the app. To promote the efficiency of SEPs, artificial intelligence technology was used for automated, individualized SEP material delivery after assessment of a patient’s diabetes management skills. Details about the app development process were reported in a previous publication [13].

After considering the needs of both the patients and clinicians, we hypothesized that the implementation of the new SEP strategy would help improve diabetes control for T1DM patients. However, a well-designed RCT is needed to assess the effectiveness of the newly developed app compared to usual care. The present protocol is proposed to serve this purpose. The detailed hypotheses of the RCT are that T1DM patients using the app, as opposed to usual care, will have better diabetes control in terms of HbA1c level, time in range (TIR), quality of life, self-efficacy, and psychological conditions.

This paper presents the details of the design of and protocol for the first RCT assessing the effectiveness of a new SEP based on mobile technology that specifically targeted the T1DM population in China. This study is innovative in that it compares the effectiveness of smartphone apps between usual care and automated, individualized app education to explore whether individualized treatment, as advocated by the latest guidelines [14], will bring any additional benefit to T1DM patients. The ultimate goal is to provide an effective and convenient approach for T1DM control and reduce the related disease burden in China, where the T1DM control status is far from optimal. The protocol of the trial is reported by following the items recommended by the Standard Protocol Items: Recommendations for Interventional Trials (SPIRIT) 2013 statement [15]. The final results will be reported after the RCT in line with the Consolidated Standards of Reporting Trials (CONSORT) 2010 Statement for reporting parallel group randomized trials [16].

## Methods

### Overview of the study design

This single-blinded, 24-week, parallel-group randomized controlled trial with a 1:1 allocation ratio will be conducted in Changsha, China. Patients with T1DM will be randomly allocated into one of two groups: automated, individualized education through an app, and artificial intelligence or routine care. The intervention will last for 24 weeks. The primary outcome will be the change in HbA1c from baseline to week 24 (see flowchart in Fig. 1).

**Fig. 1 Fig1:**
[figure not shown]
Flowchart of the trial

Outcome measurements will be collected at baseline, week 12, and week 24. The laboratory staff who test the HbA1c level; the outcome assessor who collects data on psychosocial, physiological, and anthropometric data; and the statisticians will be blinded to the treatment allocation. All the outcomes and their measurement sequences during the RCT are presented in Table 1.

**Table 1 Tab1:** The sequence of trial measurements for the primary and secondary outcomes

Timepoint	Baseline	Week 12	Week 24
**Primary outcome**			
HbA1c	×	×	×
**Secondary outcome**			
Time in range (TIR)	×	×	×
Fasting blood glucose (FBG)	×	×	×
Systolic blood pressure	×	×	×
Diastolic blood pressure	×	×	×
Total cholesterol	×	×	×
High-density lipoprotein (HDL) cholesterol	×	×	×
Low-density lipoprotein (LDL) cholesterol	×	×	×
Triglycerides	×	×	×
Body mass index (BMI)	×	×	×
Adult diabetes quality of life (A-DQOL)	×	×	×
The type 1 diabetes self-management questionnaire	×	×	×
Summary of Diabetes Self-Care Activities Assessment (SDSCA)	×	×	×
Diabetes Empowerment Scale-Short Form (DES-SF)	×	×	×
Beck’s Depression Inventory (BDI)	×	×	×
State-Trait Anxiety Inventory (STAI)	×	×	×
Patients satisfaction	×	×	×
Adverse events^a^	×	×	×

^a^Adverse events will be collected every 4 weeks during the intervention period through a telephone interview

### Setting

The trial setting is a university-affiliated tertiary hospital, the Second Xiangya Hospital of Central South University, in Changsha, Hunan, China. The study received ethics approval from the ethics committee of the Second Xiangya Hospital, Central South University (2019 Ethics Approval [Department] No. 072), and was registered as NCT04016987.

### Participants

Participants who meet the diagnostic criteria for T1DM according to the 1999 World Health Organization (WHO) report [17] will be considered eligible. Detailed inclusion and exclusion criteria are listed in Table 2. There will be no special criteria for discontinuing the allocated interventions.

**Table 2 Tab2:** Eligibility criteria

Inclusion criteria	Exclusion
1. Insulin dependence from disease onset	1. Age below 18 years or above 50 years
2. Disease duration longer than 6 months	2. Being pregnant
3. Age between 18 and 50 years old	3. Having a mental disorder
4. Positive testing for at least one of the three pancreas autoantibodies: glutamic acid decarboxylase autoantibody (GADA), insulinoma-associated-2 autoantibodies (IA-2A), zinc transporter 8 autoantibody (ZnT8A)	4. Having any other condition or disease that may hamper from compliance with the protocol or complication of the trial
5. HbA1c > 7.0%	5. Already using a smartphone app for managing diabetes
6. Being treated with multiple daily injections or insulin pump	6. Having chronic complications including diabetic retinopathy, diabetic nephropathy or diabetic foot, diabetic neuropathy
7. Owning a smartphone and are capable of sending a message through WeChat or an app	

### Sample size estimation

We propose to enroll 138 T1DM patients including withdrawals, 69 in the smartphone app group and 69 in the routine care group. The sample size estimation is based on the hypothesized changes in the primary outcome HbA1c. Details are presented below.

The primary analysis will compare the level of HbA1c between the smartphone app group and the routine care group. In a recent meta-analysis [11], data from seven RCTs that compared the difference in HbA1c between smartphone app and usual care groups were extracted, and the pooled mean difference was − 0.6%, which was used as the expected effect of this RCT. Using a two-sided hypothesis test at a 5% significance level, with an allocation ratio of 1:1, a total of 110 T1DM patients will be needed to detect a difference in HbA1c between the smartphone app group and routine care group of 0.6% with 80% power. The withdrawal rate among the RCTs included in the meta-analysis ranged from 0.0 to 26.4%, with a median of 8.4% [11]. We conservatively used a drop-out rate of 20%, yielding a total sample size of 138 (69 in the smartphone app group and 69 in the routine care group).

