## Discussion

A robust and well-designed RCT will be conducted to determine the effect of an automated, structured education intervention based on an app and artificial intelligence; it has been developed in an evidence-based and culturally tailored manner for the Chinese population for the management of T1DM. The detailed research plan of the RCT is presented in this protocol.

Although evidence had established the effect of smartphone apps in diabetes care, the majority of apps had been developed for T2DM patients and targeted at populations outside of China [10, 11]. According to an updated systematic review [11], only seven trials provided evidence on the effect of smartphone apps among T1DM patients. Pooled results (pooled MD in HbA1c − 0.49%, 95% CI − 0.94 to − 0.04%, *I*^2^ = 83.29%) showed a promising benefit for using smartphone apps to manage T1DM. However, the results from the individual trials were substantially inconsistent (MD of HbA1c varied from − 1.17% [36] to 0.41% [37]), which explained the high level of heterogeneity (*I*^2^ = 83.29%) in the meta-analysis. Furthermore, the results also indicated that the effect of smartphone apps in type 1 diabetes care was still controversial and had a low quality of the evidence [11].

Hence, whether smartphone apps will provide benefits to T1DM patients has not yet been conclusively determined. Very limited effective apps are available for T1DM patients from China. We developed a smartphone app by specifically considering the cultural background and lifestyle of the Chinese population to assist self-management and meet the need for lifelong diabetes care in T1DM patients. In this study, we seek to determine the effectiveness of the newly developed app in type 1 diabetes care compared to routine care.

Moreover, we also plan to explore whether tailoring health education materials by considering the specific knowledge gaps of each individual patient will provide some extra benefits in reducing HbA1c and improving other psychological and psychosocial outcomes. This will facilitate the development of future smartphone apps. As advocated by the latest guidelines, strategies for diabetes management should promote individualized targets and treatments [14]. By including multiple secondary outcomes, this RCT has the chance to explore the potential mechanisms of smartphone apps in improving diabetes care. This will contribute to appropriate outcome selections for future RCTs in diabetes care.

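### The sample size rests on a pooled HbA1c effect of −0.6%, but the protocol elsewhere reports −0.49% for the same seven trials, and 138 patients do not give 80% power for −0.49%

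*Protocol article*

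**What the plan says.** The Sample size estimation section of the protocol article cites a meta-analysis of seven randomised trials of smartphone app versus usual care and says that "the pooled mean difference was − 0.6%, which was used as the expected effect of this RCT". The test settings are given as follows: "Using a two-sided hypothesis test at a 5% significance level, with an allocation ratio of 1:1". The result is that "a total of 110 T1DM patients will be needed to detect a difference in HbA1c between the smartphone app group and routine care group"; the difference meant is 0.6% and the power 80%. A 20% drop-out allowance raises 110 to 138, or 69 per arm. The section describes 20% as conservative, since withdrawal in the cited trials ranged from 0.0 to 26.4% with a median of 8.4%. No SD is given.

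The Background cites the same reference and the same count of seven trials, with usual care as comparator, and reports "pooled mean difference [MD] − 0.49%, 95% confidence interval [CI] − 0.94 to − 0.04" (per cent HbA1c, I² 83.29%). The Discussion repeats it: "pooled MD in HbA1c − 0.49%, 95% CI − 0.94 to − 0.04".

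**The concern.** One source, one comparison and one set of seven trials carry two different pooled values in the same document, and the larger one drives the sample size. It is larger by 0.60/0.49 = 1.22, or 22%. Rounding does not explain the gap, because −0.49 rounds to −0.5. The document mentions no subgroup, sensitivity analysis or clinically important difference that would yield 0.6. The Sample size estimation section presents 0.6 as the pooled estimate, not as a chosen target.

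What is at stake is how a non-significant result would be read. The Discussion calls the existing evidence controversial and of low quality, with single-trial differences from −1.17% to 0.41%. In that setting a null result would be weighed against the advertised 80% power. If power at the protocol's own pooled estimate is nearer 63%, more than one such trial in three would miss a true effect of that size.

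**Working it through.** **Inputs.** From Sample size estimation: two-sided 5% test, 1:1 allocation, 80% power, difference 0.6%, 110 analysed (55 per arm), 20% drop-out, 138 randomised (69 per arm), cited median withdrawal 8.4%. From Background and Discussion: pooled difference −0.49%, 95% CI −0.94 to −0.04. The SD is not stated and is back-solved below.

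**1. The drop-out step reproduces.** 110/(1 − 0.20) = 137.5, rounded up to 138.

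**2. SD implied by the plan's 110.** With n per arm, SD = difference / [(1.960 + 0.842) × √(2/n)]. For n = 55 this is 0.6/(2.802 × √(2/55)) = 1.123 by the normal approximation. The two-sample t-test version gives 1.113, a standardised difference of 0.6/1.113 = 0.539. So 110 patients at 80% power and 0.6% are mutually consistent if the SD was about 1.11 to 1.12.

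**3. Consistency of −0.49%.** The midpoint of the quoted interval is (−0.94 − 0.04)/2 = −0.49, so that figure agrees with its own interval.

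**4. Power at 0.49% with 55 per arm.** This needs no outside SD. If 55 per arm gives 80% power at 0.6, the expected test statistic there is 2.802, and at 0.49 it is 2.802 × 0.49/0.60 = 2.288. Power = Φ(2.288 − 1.960) = Φ(0.328) = 62.9%. The t-test with SD 1.113 also gives 62.9%.

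**5. Power at 0.49% with less drop-out.** The expected statistic grows with √(n/55).

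- Withdrawal of 8.4%: 138 × 0.916/2 = 63.2 per arm; 2.288 × √(63.2/55) = 2.453; Φ(0.493) = 68.9%.
- No withdrawal: 69 per arm; 2.288 × √(69/55) = 2.563; Φ(0.603) = 72.7% (t-test with SD 1.113: 72.8%).

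| Patients analysed | Drop-out | Power at 0.49% |
|---|---|---|
| 110 | 20% (planned) | about 63% |
| about 126 | 8.4% (cited median) | about 69% |
| 138 | none | about 73% |

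**6. Scale of the gap.** For fixed power and SD, the required number scales with (0.60/0.49)² = 1.50. So 80% power at 0.49% would take about 110 × 1.50 = 165 analysed, or about 165/0.8 = 206 randomised, against 138 planned.

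**The case against.** The strongest reply is that no arithmetic in the plan is wrong. The claim is conditional, namely 80% power if the difference is 0.6%. A single SD satisfies it, and the drop-out inflation is correct. That stands. A reader might infer that the 80% figure is a miscalculation, and the documents do not support this.

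A reader might also infer that −0.6% is a proven slip and −0.49% the true pooled value. The documents favour −0.49%, which appears twice and sits at the centre of its interval. They cannot settle the matter, since −0.6% might come from another analysis in the cited source. An explanation through the trials of apps specific to type 1 diabetes does not fit, because the Sample size estimation section also counts seven trials.

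It is fair to add that 63% is the low end. It assumes the full 20% loss, which the protocol calls conservative. The Data analysis section keeps all randomised patients through multiple imputation, but imputation does not restore all the information lost, so 73% is a ceiling for this unadjusted comparison. It is also true that 0.6 lies well inside the quoted interval, and that a reported confidence interval would soften a misreading of a null result. Neither point removes the contradiction.

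Two further readings should be resisted. One is that the SD was really larger and power worse still; the documents give no SD, and one well away from 1.11 to 1.12 would not reproduce the protocol's 110. The other is that adjusting for baseline HbA1c would recover the lost power. That depends on a baseline-to-week-24 correlation the documents do not give, and on whether the implied SD belongs to the level or the change. The Sample size estimation section speaks of both, while the Overview of the study design defines the primary outcome as the change. Finally, a condensed article may leave the SD to the full protocol, so its absence is not a separate fault.

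**Conclusion.** The concern holds as an internal contradiction about the figure on which the sample size is based. The same seven-trial result is given as −0.6% where the trial is sized and as −0.49% in the Background and Discussion, without explanation. The 80% power statement holds at 0.6%, but the trial does not have that power at 0.49%. There it is about 63% under the planned drop-out, about 69% at the cited median withdrawal, and at most about 73% with complete data.

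These figures assume an unadjusted two-sample comparison at a two-sided 5% level, and that the protocol's own 110 is right for 0.6% at 80% power. Given that, the fall in power depends only on the ratio 0.49/0.60 and the number analysed, not on any SD brought in from outside.

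**What to change.** Reconcile the Background, Sample size estimation and Discussion sections against the cited meta-analysis. Then do one of the following:

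- **Use −0.49%** as the planning effect and restate power as about 63% with 110 analysed, rising to about 73% with no drop-out.
- **Keep 0.6%** as the target difference, justify it, remove the statement that it is the pooled estimate, and report power at 0.49% beside it.

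In both cases, state the SD actually used in the calculation, and whether it is the SD of the week-24 level or of the change from baseline. The sponsor should report its own figure rather than adopt the back-solved 1.11.

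Keep the target of 138. The cost is a wording correction and a less favourable stated power. No patients are added, and neither the endpoint nor the analysis changes.
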